#### Rate of loss to follow-up

In the earlier efficacy trial, the follow-up rate was 75% at two months. Primary care research participants usually have good follow-up rates although it may be lower than in the efficacy trial because of the programme being offered rather than being volunteered for. Reminders and additional attempts to contact participants may have a positive effect on retention.

#### Measurement of outcomes at follow up

Table 
2 summarises the measurement of outcomes at baseline and follow-up. Weight and waist circumference will be assessed at all time points, as will questionnaire-based measures. Clinical measures will be taken only at 3 months.

**Table 2 T2:** Summary of baseline and follow-up assessments

**Measure**		**Month of treatment**				
	**Baseline**	**3 (End of active treatment phase)**	**6**	**12**	**18**	**24**
Weight	X	X	X	X	X	X
Waist circumference	X	X	X	X	X	X
Questionnaire-based measures	X	X	X	X	X	X
Blood pressure	X	X				
Blood cholesterol/LDL/glucose levels	X	X				

#### Qualitative interviews

We will conduct semi-structured individual telephone interviews with a purposive sample from the intervention group (n ~ 20) at 3 and 6 month follow-up to explore self-reported barriers to, and facilitators of, compliance with each of the ‘tips’.

### Compliance

The intervention requires little supervision or contact with health professionals, and the instructions are simple. In the pilot study, the ease of the intervention was well received by the participants, even those with fewer years of education, who compared it favourably with other weight loss programmes. Patients randomised to the intervention will be given logbooks with a simple system of recording daily tip adherence, and will be asked to return completed books to the researchers via post. This data will provide some idea of the level of compliance and will be presented descriptively.

### Methods for protecting against sources of bias

It is not possible to blind participants, but follow-up at the end of the active treatment period (3 months) will be with a health professional blind to the intervention allocation where possible. Practical reasons (e.g. unavailability of the appropriate health professional) may prohibit blinded follow ups for all patients at 3 months. Given that the primary outcome is at 3 months, and the use of pre-dominantly objective measures, it was felt that blinding was un-necessary after the 3 month follow up. A detailed analysis plan will be developed prior to the analysis and the data-analyst will remain blind to allocation until completion of the final analyses. We will limit non-response bias through maximising follow-up using reminder phone calls prior to their follow-up appointments. Number of contact attempts and reason for withdrawing from follow-up will be recorded to facilitate statistical analyses of non-response bias. Non-attenders will also be asked to provide a self-report of their weight over the phone. Selection bias arising from recruitment of patients with recorded BMI data is largely unavoidable but comparison of sample characteristics with those of the wider (obese) population obtained from Health Survey for England data will allow us to assess the extent of this bias.

## Statistics and data analysis

### Sample size and assumptions

The exploratory trial of the intervention 
[15] showed a difference of weight change between baseline and 8 weeks of 1.41 kg (SD = 1.9) between the intervention and control groups. As the trial population may be more heterogeneous, and the outcome is measured 4 weeks later, we powered the study to detect a mean difference in weight change of 1.0 kg, with a standard deviation of 2.5. Based on a two sample test, 132 evaluable participants per arm are required to detect such a difference with 90% power, and a significance level of 5%. This sample size has been calculated using the statistical software STATA. However, a clustering effect may occur in the intervention arm due to different health professionals delivering the intervention in each practice. Power calculation formulae for a partially clustered design have been reported 
[42]. Based on an average cluster size of 13 evaluable participants (those completing 3 months follow-up), and an ICC of 0.05 
[43] in the intervention arm, a total of 364 evaluable patients at 3 months (26 in each of the 14 practices) would provide 92% power to detect such a difference. This should insure the power stays above 90% even with a small imbalance in cluster size between practices 
[44]. Allowing for 30% attrition (26% observed in the pilot study at 8 weeks), 260 participants would need to be recruited by arm, or 520 in total.

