### Randomisation

The unit of randomisation is the patient. Randomisation will be done by telephoning a central randomisation service (Health Service Research Unit at Aberdeen) ensuring allocation concealment, after the participant has provided informed consent and baseline data. A computer-generated list of random permuted blocks of varying sizes will be used. Randomisation will be stratified by practice to ensure socioeconomic balance between randomised groups.

Patients randomised to the intervention group will be given the 10TT leaflet and self-monitoring log book to use in the acquisition phase, with additional brief information on the idea of forming healthy habits. Following this appointment they will be sent a booster letter with a second copy of the 10TT leaflet and can request a second log book if they would like one.

Patients randomised to the control group will be referred to the Practice’s usual care. We will ask participating Practice’s to inform us of what their usual care consists of, and this will be recorded. This will at least be a referral to a practice-based health professional not involved in the trial for a discussion on healthy eating, but in some Practices, may also be a referral to Weight Watchers.

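### The 92% power and the 90% floor assume no clustering in the control arm, although usual care is also given by practice professionals and varies by practice; power should be stated conditionally and the primary model should cover both arms.

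*Protocol article*

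**What the plan says.** Under Sample size and assumptions, the protocol article gives this reason for allowing for clustering: "a clustering effect may occur in the intervention arm due to different health professionals delivering the intervention in each practice". It uses partially clustered formulae with 13 evaluable patients per cluster and an ICC of 0.05 in the intervention arm. It concludes that "a total of 364 evaluable patients at 3 months (26 in each of the 14 practices) would provide 92% power", and adds that power should remain over 90% under slightly unequal cluster sizes.

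The Randomisation section describes what controls receive: "This will at least be a referral to a practice-based health professional not involved in the trial for a discussion on healthy eating". It adds that this "in some Practices, may also be a referral to Weight Watchers". Allocation is by individual patient, stratified by practice, so every practice contributes to both arms.

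Under Data analysis, the primary comparison of 3-month weight change is a random-effects linear regression with clustering by the professionals who deliver 10TT, in the intervention arm. A further sentence says that random-effects regression will also be used to look into clustering by practice. It does not say that this enters the primary comparison.

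**The concern.** A partially clustered calculation treats controls as independent patients. That suits a comparator with no grouped delivery, such as the no-treatment control of the earlier volunteer trial described in the Background. Here the control arm also receives advice from practice staff, and its content depends on the practice. The plan's own reason for clustering, that different professionals act in different practices, therefore applies to controls too, and the article gives no reason for a control ICC of exactly zero.

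Two things are at stake. The first is the power claim and its 90% floor, which has little margin. The second matters more: the primary model carries the same assumption, so the standard error of the main result could be wrong.

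**Working it through.** **Inputs from Sample size and assumptions.** Difference 1.0 kg and SD 2.5, so variance 6.25; 5% significance, which reproduces the stated 132 per arm at 90% power when two-sided; 14 practices; 13 evaluable per practice per arm, so 182 per arm; ICC 0.05 in the intervention arm.

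**Inputs that must be assumed.** The control-arm ICC (range 0 to 0.05), the correlation c between the two arms' cluster effects within a practice (range 0 to 1), and one cluster of 13 per practice in the control arm.

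**The plan's figure.** The design effect is 1 + (13 − 1) × 0.05 = 1.6 in the intervention arm and 1 in the control arm.

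- Variance of the difference = (6.25/182) × (1.6 + 1) = 0.0893; SE = 0.2988.
- Power = Φ(1/0.2988 − 1.96) = 91.7%, which matches the stated 92%.
- Recruitment = 182/0.7 = 260 per arm, which also matches.

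**Control clustering independent of the intervention arm.** Variance = (6.25/182) × (1.6 + 1 + 12 × control ICC). If the planned model still reports an SE near 0.2988, its type I error is about 2 × [1 − Φ(1.96 × 0.2988/true SE)].

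| Control ICC | True SE | Power | Type I error, intervention-only model |
|---|---|---|---|
| 0 | 0.2988 | 91.7% | 5.0% |
| 0.01 | 0.3056 | 90.5% | 5.5% |
| 0.02 | 0.3123 | 89.3% | 6.1% |
| 0.03 | 0.3188 | 88.0% | 6.6% |
| 0.05 | 0.3315 | 85.5% | 7.7% |

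Power drops below 90% at a control ICC between 0.01 and 0.02. In the last row, a t reference on 26 degrees of freedom gives 82.7% instead of 85.5%.

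**ICC 0.05 in both arms, effects correlated within practice.** Between-cluster variance is 0.05 × 6.25 = 0.3125 and within-cluster variance is 5.9375. The part shared by the arms cancels from the within-practice contrast:

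Variance = 2 × 5.9375/182 + 2 × (0.3125/14) × (1 − c).

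| c | SE | Power if practice is modelled |
|---|---|---|
| 0 | 0.3315 | 85.5% |
| 0.25 | 0.3142 | 88.9% |
| 0.33 | 0.3085 | 90.0% |
| 0.5 | 0.2959 | 92.2% |
| 1 | 0.2554 | 97.5% |

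At c of about 0.46 the true SE equals the planned 0.2988. Above that, the intervention-only model reports an SE that is too large; at c = 1 it is 0.2988 against a true 0.2554. Below it, the reported SE is too small.

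**The case against.** The strongest reply is that the 92% is not a miscalculation. The partially clustered assumption is stated openly and rests on cited formulae. This stands: the dispute is about an input.

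Second, a reader might infer that the trial's power is really about 85% and its type I error 7.7%. The document does not support that. The ICC of 0.05 is given for the intervention arm only, and carrying it to controls is an assumption. A referral may well produce a weaker provider effect than a 30-minute scripted session. Nor does the article say that one professional sees all of a practice's controls. With two control providers per practice (clusters of 6.5, design effect 1 + 5.5 × 0.05 = 1.275), the variance is (6.25/182) × 2.875 = 0.0987, power 88.9% and type I error about 6.2%. With three, power is about 90%.

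Third, both arms share the practice, its population and its equipment. The control professional is by design not the trial's deliverer, which argues against a shared provider effect, but a shared practice effect remains possible and would raise power if modelled. This also stands, and it is why 85% can only be one case among several.

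Fourth, the article promises to look at practice clustering and defers detail to a later analysis plan. That helps only in part. The primary model is named, with its random effect in one arm, and the practice sentence does not amend it.

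**Conclusion.** The point holds as a matter of unsupported assumption and model specification. The 92% follows from its inputs, but it and the 90% floor depend on a control ICC of zero, which fits poorly with the control care that the article itself describes.

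Across the assumptions above, power runs from about 85% (ICC 0.05 in both arms, independent effects, one control provider per practice) through 92% (no control clustering) to about 97% (practice effects fully shared and modelled). Nothing in the document locates the trial within that range, so neither the unconditional floor nor a flat replacement figure is justified.

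The conclusion about the model does not depend on where in the range the trial lies. An intervention-only random effect misstates the standard error whichever kind of control-arm clustering dominates. Independent provider effects make it too small, with type I error about 6% at control ICC 0.02 and at most about 7.7% at 0.05. A largely shared practice effect makes it too large.

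**What to change.** In the primary model, include practice, which is the stratification factor, for both arms, and add a practice-by-arm random effect in place of clustering in the intervention arm only. Settle this before the analysis.

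In the sample size section, state power as conditional on the control ICC and the cross-arm correlation: about 85% with independent effects at ICC 0.05 in both arms, 92% with no control clustering, and higher if practice effects are largely shared. Remove the unconditional assurance of more than 90%.

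N stays at 520, and practice is already known for every patient through stratification. The cost is a less favourable stated power in some scenarios, and one or two extra variance terms that must be estimated from only 14 practices.

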### Data analysis

Baseline characteristics will be reported by each arm using descriptive statistics. A random effects linear regression model accounting for clustering by health professionals delivering the intervention in the intervention arm will be used to compare the weight change at 3 months from baseline between the two groups. This analysis will be adjusted for baseline weight which should make the statistical analysis more efficient. Random effects linear regression model will also be used to investigate the clustering effects due to practice.

Bias due to missing data will be investigated. If required, sensitivity of the results to missing data will be investigated using different approaches for handling missing data, including adjusting for predictors of missingness that are related to the outcome, multiple imputation and baseline observation carried forward. The possibility that data may not be missing not at random (MNAR) will also be considered and if necessary approaches that can handle MNAR data will be used as part of the sensitivity analysis 
[45]. Additionally, the scope of incorporating information on reasons for dropout in the analyses will also be explored.

Secondary outcomes will be compared between the intervention groups using appropriate regression models taking account of clustering. Subgroup analyses will investigate intervention effects by gender, age (in tertiles), baseline BMI (<35 vs. ≥35), ethnic origin (white vs. other) and deprivation (tertiles of postcode-based Index of Multiple Deprivation) as part of secondary analyses. Results from all secondary analyses will be considered as exploratory.

The primary aim of the trial is to evaluate the effectiveness of offering the intervention; therefore all analyses will be performed on an intention to treat basis. A detailed analysis plan will be prepared nearer the data analysis stage.

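### The 92% power is a large-sample figure; a test that holds 5% on 14 intervention clusters has about 90%, so the assurance of more than 90% under imbalance has essentially no margin (minor).

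*Protocol article*

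**What the plan says.** All the planning figures are in the protocol article under Sample size and assumptions. The authors write that "we powered the study to detect a mean difference in weight change of 1.0 kg, with a standard deviation of 2.5", and obtain 132 evaluable patients per arm for 90% power at the 5% level, ignoring clustering. They then allow for clustering in one arm only, because "a clustering effect may occur in the intervention arm due to different health professionals delivering the intervention in each practice". With an average of 13 evaluable patients per cluster and an ICC of 0.05, they state that 364 evaluable patients (26 in each of 14 practices) "would provide 92% power to detect such a difference". The next sentence draws the assurance at issue: "This should insure the power stays above 90% even with a small imbalance in cluster size between practices". No CV of cluster size is given, and degrees of freedom are not mentioned. The total is raised to 520 for 30% attrition.

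Under Data analysis, the primary model is named: "A random effects linear regression model accounting for clustering by health professionals delivering the intervention in the intervention arm will be used". It is adjusted for baseline weight, which the authors expect to improve efficiency. Detail is left to a later analysis plan.

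**The concern.** The step from 132 to 182 evaluable patients per arm is presented as giving a two-point cushion over 90%, and that cushion is what the authors rely on to absorb unequal cluster sizes. The sizing implies one intervention cluster per practice, so the variance of the intervention-arm mean has to be estimated from 14 cluster means, on about 13 degrees of freedom. A calculation that treats this variance as known overstates the power of any test that keeps its level. If the cushion is used up by that correction alone, nothing is left for imbalance. The 5% level and the assurance of more than 90% power are both stated in the same paragraph, and the question is whether they hold together.

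**Working it through.** **Inputs**, all from Sample size and assumptions: difference 1.0 kg; SD 2.5 kg, taken as the total SD in each arm; ICC 0.05 in the intervention arm only; 364/2 = 182 evaluable per arm; 182/13 = 14 intervention clusters. A two-sided 5% level is inferred, because it reproduces the 132 per arm: 2 × 6.25 × (1.960 + 1.282)² = 131.3, rounded up to 132. No credit is taken for baseline adjustment, as in the plan.

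**1. The plan's own figure.**
- Design effect, intervention arm: 1 + 12 × 0.05 = 1.6
- V1 (intervention mean) = 6.25 × 1.6/182 = 0.0549
- V2 (control mean) = 6.25/182 = 0.0343
- SE = √(0.0549 + 0.0343) = 0.2988
- Power by z = Φ(1/0.2988 − 1.960) = Φ(1.387) = 91.7%, which rounds to the stated 92%
- Attrition: 364/0.70 = 520, as stated

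**2. The same inputs with finite degrees of freedom.**
- Satterthwaite df = (V1 + V2)²/(V1²/13 + V2²/181) = 33.4
- Two-sided 5% critical value of t: 2.034 instead of 1.960
- Power from the noncentral t: 90.1%

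This correction alone takes 91.7 − 90.1 = 1.6 points.

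**3. Unequal clusters.** The protocol gives no CV, so a range is assumed. With size weights the design effect is 1 + ((1 + CV²) × 13 − 1) × 0.05. Random-effects weights lose a little less, and where two figures appear below, the range runs from size weights to random-effects weights.

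| CV of cluster size | Power by z, size weights | Power by t |
|---|---|---|
| 0 | 91.7% | 90.1% |
| 0.1 | 91.7% | 90.1% |
| 0.2 | 91.5% | 89.8% to 89.9% |
| 0.3 | 91.1% | 89.4% to 89.7% |
| 0.4 | 90.7% | 88.9% to 89.4% |
| 0.5 | 90.1% | 88.2% to 88.9% |

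The t-based figure crosses 90% at a CV between 0.1 and 0.2 (about 0.15 with size weights).

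**4. Simulation check.** 40,000 trials per setting, REML random effects in the intervention arm with separate arm variances, 14 clusters totalling 182.

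| Cluster sizes | Type I error, z | Type I error, Satterthwaite t | Power, z | Power, Satterthwaite t |
|---|---|---|---|---|
| All 13 | 5.6% | 4.9% | 91.5% | 90.3% |
| 8 to 18 (CV 0.22) | 5.6% | 4.9% | 91.1% | 89.6% |
| 5 to 23 (CV 0.40) | 5.6% | 4.9% | 90.4% | 89.0% |

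A separate simulation of 20,000 trials per setting put the type I error of the z-read REML test at up to 5.9%.

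**5. What baseline adjustment could return.** Suppose baseline weight explains a fraction R² of the variance of weight change (an assumption; the protocol gives none). Both variances are multiplied by 1 − R². At CV 0.3, t-based power becomes 89.7% to 90.0% for R² = 1%, 90.0% to 90.3% for 2%, and 90.9% to 91.1% for 5%.

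**The case against.** The strongest reply is that nothing was miscalculated. The chain from 132 per arm to 364 evaluable, 92% and 520 reproduces, and on the same large-sample basis power stays above 90% up to a CV of about 0.5. That stands: the 92% is a valid large-sample figure, and a reader who inferred an arithmetic slip would be wrong.

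Second, the protocol does not commit to a normal reference distribution. It names a random effects linear regression and defers detail to an analysis plan, where the estimation method and degrees of freedom normally belong. That also stands. Their absence here is not a fault, and the documents do not support an inference that the primary test will run above 5%. The type I figures show only what a z-read analysis would cost. The power assurance, however, is not deferred: it is stated as a property of the design.

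Third, the planned baseline adjustment is slack that the calculation does not use, and explaining about 2% of the variance would restore 90% at CV 0.3. This limits the point without removing it, because the sample size section neither invokes the adjustment nor assumes a correlation.

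Fourth, the degrees of freedom assume one deliverer per practice. The intervention section speaks of nurses or health care assistants in each centre. With two deliverers per practice (28 clusters of 6.5) t-based power would be about 94%. But the plan's own sizing, 13 per cluster and 26 per practice across two arms, is one intervention cluster per practice.

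Finally, the effect of few clusters should not be overstated. Between-cluster variation is (0.05 × 6.25/14)/0.0549 = 0.0223/0.0549 = 41% of the variance of the intervention mean, so it is not the larger part.

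**Conclusion.** The point holds as a minor one. On the plan's own inputs, a test that holds the 5% level has about 90.1% power with equal clusters, 89.8% at CV 0.2, 89.4% to 89.7% at CV 0.3 and about 89% at CV 0.4. The 5% level and the assurance of more than 90% therefore do not hold together once the CV reaches about 0.15, and the assurance has essentially no margin before that.

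This rests on one intervention cluster per practice, clustering in the intervention arm alone, SD 2.5 and ICC 0.05 as stated, and no gain from baseline adjustment. A reader might infer that the trial is underpowered or needs more patients. The figures do not support that: for small imbalance the shortfall from 90% is under about 0.5 points. Nor should 89% be quoted for small imbalance, since it needs a CV of about 0.4.

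**What to change.** Under Sample size and assumptions, describe power as about 90% with equal clusters and slightly below 90% with imbalance, and state the CV of cluster size that is assumed. Either remove the assurance that power remains above 90%, or keep it and support it with an explicit assumed gain from baseline-weight adjustment.

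Under Data analysis, or in the analysis plan, specify that the primary model is fitted by REML and the arm effect tested with Satterthwaite or Kenward-Roger degrees of freedom.

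The cost is a sentence or two and a slightly less favourable power figure. The sample size does not change.

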### Data analysis

Baseline characteristics will be reported by each arm using descriptive statistics. A random effects linear regression model accounting for clustering by health professionals delivering the intervention in the intervention arm will be used to compare the weight change at 3 months from baseline between the two groups. This analysis will be adjusted for baseline weight which should make the statistical analysis more efficient. Random effects linear regression model will also be used to investigate the clustering effects due to practice.

Bias due to missing data will be investigated. If required, sensitivity of the results to missing data will be investigated using different approaches for handling missing data, including adjusting for predictors of missingness that are related to the outcome, multiple imputation and baseline observation carried forward. The possibility that data may not be missing not at random (MNAR) will also be considered and if necessary approaches that can handle MNAR data will be used as part of the sensitivity analysis 
[45]. Additionally, the scope of incorporating information on reasons for dropout in the analyses will also be explored.

Secondary outcomes will be compared between the intervention groups using appropriate regression models taking account of clustering. Subgroup analyses will investigate intervention effects by gender, age (in tertiles), baseline BMI (<35 vs. ≥35), ethnic origin (white vs. other) and deprivation (tertiles of postcode-based Index of Multiple Deprivation) as part of secondary analyses. Results from all secondary analyses will be considered as exploratory.

The primary aim of the trial is to evaluate the effectiveness of offering the intervention; therefore all analyses will be performed on an intention to treat basis. A detailed analysis plan will be prepared nearer the data analysis stage.

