#### Clinical measures

Blood pressure and blood cholesterol/LDL/glucose levels will be assessed with standard practice procedures. Blood samples are being analysed within the NHS (as opposed to by a single laboratory) so there may be some variation in assessment. Due to practical considerations we are measuring random glucose rather than fasting, which may overestimate risk in our sample.

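### The stated primary model omits practice, the only named stratification factor, and models clustering in the intervention arm alone, so its standard error can be wrong

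*Protocol article*

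**What the plan says.** Patients are randomised individually within 14 practices. The Randomisation section says: "Randomisation will be stratified by practice to ensure socioeconomic balance between randomised groups". No other stratification factor is named.

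The Data analysis section gives the primary model: "A random effects linear regression model accounting for clustering by health professionals delivering the intervention in the intervention arm will be used to compare" weight change from baseline at 3 months. Baseline weight is its only stated covariate. The section then adds: "Random effects linear regression model will also be used to investigate the clustering effects due to practice". That brings practice into the analysis, but does not put it in the primary comparison.

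The one-arm cluster effect follows the Sample size section, which expects clustering in the intervention arm because different health professionals deliver the intervention. The calculation is described thus: "Based on an average cluster size of 13 evaluable participants (those completing 3 months follow-up), and an ICC of 0.05" in that arm, so that "a total of 364 evaluable patients at 3 months (26 in each of the 14 practices) would provide 92% power". With 26 evaluable patients per practice and clusters of 13, each practice supplies one intervention-arm cluster.

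Control patients go to usual care. The Randomisation section describes this as at least a discussion with a member of practice staff outside the trial, with some practices also referring to a commercial weight-loss programme.

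**The concern.** An effect of practice on weight change that is common to both arms cancels from a comparison made within practices. The stated model does not know this. In the intervention arm, provider and practice coincide under the plan's own assumptions, so the provider random effect absorbs the practice variation and charges it to the treatment contrast. In the control arm the same variation goes into the residual. The SE is then too wide, and the precision gained by stratifying is lost.

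Practice differences are plausible on the protocol's own account. Practices are chosen to span urban and rural areas and to include deprived or ethnically diverse populations, and stratification is justified by socioeconomic balance.

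The one-arm specification also has a risk in the other direction. If usual care clusters by provider within practice, the model has no term for it, and the SE can be too narrow.

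**Working it through.** **Inputs from the Sample size section.** "we powered the study to detect a mean difference in weight change of 1.0 kg, with a standard deviation of 2.5" (σ² = 6.25); 14 practices; 13 evaluable patients per arm per practice, so 182 per arm; intervention-arm ICC 0.05; attrition 30%. Significance is taken as two-sided 5%.

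**The plan's own figures reproduce.**
- Unclustered: 2 × (1.96 + 1.2816)² × 6.25 / 1² = 131.3, so 132 per arm.
- Partially clustered: variance = 6.25 × (1 + 12 × 0.05)/182 + 6.25/182 = 0.0893, SE 0.299. Power = Φ(1/0.299 − 1.96) = 91.7%, against 92% stated.
- Attrition: 364/0.70 = 520.

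**Assumptions added here.** Let p be the practice ICC shared by both arms, h the provider ICC in the intervention arm and c the provider ICC in the control arm. Only h = 0.05 is in the protocol. The residual share e = 1 − p − max(h, c) is the same in both arms. (Hence the SE of 0.296 in the first row below: with c = 0 the control-arm variance is slightly under 6.25.)

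**Formulas.**
- True variance of the contrast: 6.25 × [(h + c)/14 + 2e/182]. The practice share p cancels.
- Variance the stated model targets: 6.25 × [(p + h)/14 + e/182 + (p + c + e)/182].
- Type I error = 2[1 − Φ(1.96 × SE_model/SE_true)].
- Power of the stated model = Φ[(1 − 1.96 × SE_model)/SE_true]. Power with practice added = Φ(1/SE_true − 1.96).

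**Worked case, p = 0.05, h = 0.05, c = 0 (e = 0.90).**
- True variance = 0.3125/14 + 2 × 5.625/182 = 0.0841, SE 0.290.
- Model variance = 0.625/14 + 5.625/182 + 5.9375/182 = 0.1082, SE 0.329.
- Ratio 1.134.

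| p | h | c | True SE | Model SE | Ratio | Type I error | Power, stated model | Power, practice added |
|---|---|---|---|---|---|---|---|---|
| 0 | 0.05 | 0 | 0.296 | 0.296 | 1.000 | 5.0% | 92.2% | 92.2% |
| 0.02 | 0 | 0 | 0.259 | 0.277 | 1.069 | 3.6% | 96.1% | 97.1% |
| 0.02 | 0.05 | 0 | 0.294 | 0.310 | 1.054 | 3.9% | 91.0% | 92.6% |
| 0.05 | 0 | 0 | 0.255 | 0.299 | 1.170 | 2.2% | 94.8% | 97.5% |
| 0.05 | 0.05 | 0 | 0.290 | 0.329 | 1.134 | 2.6% | 89.0% | 93.2% |
| 0 | 0.05 | 0.05 | 0.331 | 0.299 | 0.901 | 7.7% | 89.4% | 85.5% |
| 0.02 | 0.05 | 0.05 | 0.329 | 0.312 | 0.948 | 6.3% | 88.1% | 85.9% |
| 0.05 | 0.05 | 0.05 | 0.326 | 0.331 | 1.016 | 4.6% | 85.8% | 86.5% |

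In the rows with p = 0 or 0.02 and control clustering, the stated model's higher power comes only from an SE that is too small.

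**Simulation (10,000 trials per scenario, balanced practices, critical value 1.96).** The comparison model has practice plus a practice-by-arm random effect.
- p = 0.05, h = 0.05, c = 0: stated model type I error 3.0%, power 88.6%. With practice added, 5.3% and 92.0%.
- p = 0 or 0.02, h = c = 0.05: stated model type I error 8.5% and 7.6%. With practice added, 6.2% and 6.9%. Part of the excess is the normal critical value with 14 clusters: at p = 0, h = 0.05, c = 0 the stated model is correctly specified and still runs at 5.6%.
- Practice intercept alone, provider effect dropped: type I error 8.8–8.9% when h = 0.05 and c = 0.
- No practice variance, h = 0.05, c = 0: power 91.7% for the stated model and 91.2% with practice added.

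**The case against.** The strongest reply has four parts.

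- **A detailed analysis plan is promised, and practice clustering is to be investigated.** The exact random-effects structure is often settled in such a plan, and this is a condensed article. That lowers the severity. It does not remove the point, because the article already states the primary model's outcome, covariate, cluster term and arm, and practice is not among them.
- **The intervention-arm effect is right for this design.** This stands. It matches the sample-size basis, and dropping it would be worse than the present plan.
- **The size is unknown.** This stands too. No practice ICC is given, and the outcome is weight change adjusted for baseline weight, so stable differences in weight level between practices largely drop out. At a practice ICC of 0.02 or below the excess width is at most about 7%.
- **A shared practice effect makes the test conservative, not liberal.** That is true when control care does not cluster. It is not assured otherwise.

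Three stronger readings are tempting, and the documents do not support them.

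- A reader might infer that the SE is usually too wide. The protocol describes control care that is given in the practice and can differ between practices, and this pushes the SE the other way.
- A reader might set all of the 0.05 ICC at practice level and conclude that 1 − 0.0653/0.0893 = 27% of the effective sample is lost. The protocol assigns that ICC to providers in the intervention arm, so this moves a figure to a place where the protocol does not put it.
- A reader might extend the point to the blood markers, since "Blood samples are being analysed within the NHS (as opposed to by a single laboratory) so there may be some variation in assessment". But laboratories are not tied to practices in the text, the wording for secondary outcomes is general enough to allow a practice term, and all secondary analyses are labelled exploratory.

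**Conclusion.** The point holds conditionally. The stated primary model does not include the factor by which randomisation is stratified, and it allows for clustering in one arm only. Whether its SE is right depends on quantities that the protocol does not give:

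- practices differ in both arms, no control-arm clustering: too wide, by about 5–7% at practice ICC 0.02 and 13–17% at 0.05;
- practice and provider ICCs both 0.05, no control-arm clustering: power about 88–89%, below the 90% the design means to protect, against about 92% in simulation with practice added (93% by formula);
- provider ICC 0.05 in both arms, practice ICC 0 to 0.02: too narrow, with type I error about 6–8%;
- no practice variance and no control-arm clustering: correct.

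These sizes assume 14 equal practices with 13 evaluable patients per arm and a total SD of 2.5 kg. This is an improvement that should be made, at almost no cost. It is not a flaw that invalidates the trial.

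**What to change.** In the primary model, add practice as a fixed effect or as a random intercept common to both arms. Keep baseline weight and the health-professional (practice-by-arm) random effect. Do not replace that effect with practice alone: type I error is then about 9% when provider effects exist. State how provider clustering in the control arm is handled. A practice-by-arm effect covering both arms would do this; if the effect is kept to the intervention arm, the reason should be given.

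The cost is a sentence or two in the analysis section and the analysis plan, settled before the data are analysed. Practice is already recorded for every patient through the stratification. If practices turn out not to differ, the simulated loss of power is under one percentage point (91.7% to 91.2%).
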